#### **8.6. Source data**

Biological reports results with normal range values will be considered as source data.

## **9. SELECTION AND WITHDRAWAL OF PARTICIPANTS**

### **9.1. Selection criteria**

#### **9.1.1. Demographic characteristics**

- Male or female aged  $\geq 35$  years and  $\leq 80$  years,
- BMI between 25-40 Kg/m^2 inclusive (stable body weight),
- BMI range (25-40 Kg/m^2) could be modified in countries where definition of overweight is different. It will be specified if needed.

#### **9.1.2. Medical and therapeutic criteria**

- Type 2 diabetic outpatients diagnosed according the WHO criteria (see appendix 4).
- Currently treated in monotherapy with a sulfonylurea at stable and well-tolerated dose for at least 3 consecutive months prior to the selection visit. The sulfonylurea dose must be  $\geq 50\%$  of the maximal recommended dose according to local monography. If the sulfonylurea dose is below 50%, the investigator should give a justification.
- Not optimally controlled according to the last available HbA1c value under sulfonylurea treatment likely to fit in with inclusion criteria.
- Without severe diabetic complications which according to the investigator could interfere with the efficacy or safety evaluation of the study.
- Able to comply with the study procedures and follow the study instructions particularly to fill in the diary card.

#### **9.1.3. Informed consent**

Obtained as described in section 17.3. of the protocol.

### **9.2. Non-selection criteria**

#### **9.2.1. General criteria**

- Unlikely to be compliant to study medication and visits.
- Pregnancy, breastfeeding or possibility of becoming pregnant during the study without effective contraception (investigator's judgement).
- Drug and/or alcohol abuse and patients at risk for acute alcoholic poisoning.
- Participation in another study at the same time or within 3 months prior to selection, or participant already enrolled in the present study.
- Major surgery planned during the study period.

#### **9.2.2. Medical and therapeutic criteria**

- Type 1 diabetes.
- Known Latent Autoimmune Diabetes in Adults (LADA).
- Type 2 diabetes treated in the previous 3 months with an oral hypoglycaemic agent (OHA) other than a sulfonylurea.
- Type 2 diabetes treated with more than 1 OHA in the previous 3 months.
- Insulin treatment in the previous year, except short term treatment for exceptional reason such as surgery.
- Any expected indication of chronic insulin treatment during the study ( $> 7$  days).

- Decreasing body weight  $\geq 5\%$  or body weight loss of at least 4 kg in the previous 3 months.
- Dyslipidaemia treated with a lipid medication modified during the previous 3 months or uncontrolled dyslipidaemia requiring a lipid medication or an adaptation of lipid medication dosage at inclusion or in the 2 months following the inclusion.
- Contraindication to treatment by pioglitazone (see appendix 5: the summary of pioglitazone product characteristics) i.e.:
  - o Known hypersensitivity to pioglitazone or to any of the components.
  - o Heart failure or history of cardiac failure (NYHA grade I to IV; see appendix 14).
  - o Hepatic impairment or other evidence of liver disease.
  - o Combination with insulin.
- Contraindication to treatment by benfluorex (as referred in the product characteristics, see appendix 6) i.e.:
  - o Chronic pancreatitis.
  - o Known hypersensitivity to benfluorex hydrochloride or to one of the components.
- Uncontrolled and clinically significant disease or known malignancy that could interfere with the conduct of the study limit life expectancy or require prohibited treatment (including unstable angina).
- Recent major cardiovascular event in the previous 6 months (myocardial infarction, stroke, acute ischemia).
- High blood pressure levels: Sitting systolic blood pressure  $> 180$  mmHg or sitting diastolic blood pressure  $> 100$  mmHg. This criterion must be rechecked at inclusion, if the values are still over these limits, the patient must not be included.
- Active known retinopathy with neo-vascularisation and/or sight-threatening macular oedema. The patient may be selected only if the retinopathy has been stable for at least 6 months following laser therapy.
- Acute or chronic condition apart from type 2 diabetes that would compromise end-points evaluation: e.g. all factors/diseases that interfere with the HbA1c analysis (serious anaemia, haemoglobinopathy, haemolysis, blood donation in the previous 12 weeks).
- History of acute pancreatitis.

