Furthermore, the only contraindications to treatment with benfluorex are currently: individual hypersensitivity to benfluorex chlorhydrate or to one of its components, and chronic pancreatitis. In addition, treatment with benfluorex does not require any specific monitoring for safety. Its combination to sulfonylureas should therefore be a good alternative to the other options in term of addition of agents acting on insulin sensitivity.

Two TZD (rosiglitazone and pioglitazone) are currently available on the market, the most prescribed in Europe being rosiglitazone. Since pioglitazone is less deleterious than rosiglitazone in regard to LDL cholesterol and serum triglycerides levels (21), pioglitazone will be the TZD used in this study.

The objective of this study is to demonstrate that benfluorex in combination with sulfonylurea allow to obtain a comparable glycaemic control in type 2 diabetic patients over 1 year in comparison to pioglitazone both treatments given in combination with sulfonylureas and when the sulfonylurea alone at maximal tolerated dose is not sufficient to reach therapeutic targets. A secondary objective, related to efficacy, is to demonstrate the superiority of benfluorex on LDL cholesterol plasma level.

All pre-clinical and clinical data are presented in the Investigator's Brochure n° 3 (22).

Benfluorex is registered in more than 50 countries and is marketed in 28 countries under different trade names: Mediator® in France, Portugal, Morocco and Vietnam, Lipophoral® in Greece, Medi axial® in Malaysia, Hong Kong and Singapore, Lipascor® in Argentina and Venezuela.

The study will be conducted in compliance with the protocol, Good Clinical Practice (GCP) and the applicable regulatory requirement.

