### 8.3. Measures to minimise bias

This is a multicentre, international, randomised, double-blind, double-dummy, parallel group study.

The following methods will be used to protect the blinding vis-à-vis the participants and the investigators:

- The tablets of benfluorex and benfluorex placebo will have the same aspect (size, colour) and taste. The capsules of pioglitazone and pioglitazone placebo will also be strictly identical.
- All the packaging (blisters, boxes, labels) will be strictly identical between the two treatment groups.
- In each group, patients will receive a product and the placebo of the other drug (in the benfluorex group: 3 tablets of benfluorex and 1 capsule of pioglitazone placebo will be administered per day, and in the pioglitazone group: 3 tablets of benfluorex placebo and 1 capsule of pioglitazone will be administered per day).
- The investigator will provide the CRO in charge of IVRS with all data needed for the evaluation of the dose level increase/decrease. The CRO in charge of IVRS will be responsible for the management of dose level increase/decrease according to the treatment group following the specific procedures described below.
- Sealed code list will be available at the I.R.I.S. emergency desk. No envelop with the code will be available in centres. The Adjudication Committee is blinded. The management of the blinding system is described in the section section 8.4.3. “*Management of blinding systems*”.
- Treatments will be allocated under the responsibility of the CRO responsible for the **Interactive Voice Response System (IVRS)** by non-adaptative, centralised, balanced (1:1), stratified randomisation, according to country and HbA1c ( $\leq 8\%$  or  $> 8\%$ ) at W0.

The structure responsible for designing the randomisation lists will be the Biometrics Direction of I.R.I.S..

All the efficacy and safety laboratory measurements will be analysed by a **central laboratory** in blind of the treatment allocated.

Circumstances under which the code is to be broken are described in section 8.4.3. “*Management of blinding systems*”.

All the echocardiographies will be assessed by a central reading structure in blind of the treatment assignment.

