| Appearance, colour                       | White, round                                                                                                                                                                                                                              | White, round                                                                                                                                                                                                                              |                                    |
| Composition                              | benfluorex hydrochloride                                                                                                                                                                                                                  | lactose monohydrate                                                                                                                                                                                                                       |                                    |
|                                          | Excipients : maize starch, sodium hydrogen carbonate, carmellose sodium, white beeswax, titanium dioxide, ethylcellulose, glyceryl oleate, polysorbate 80, povidone, sucrose, anhydrous colloidal silica, magnesium stearate, talc | Excipients : maize starch, sodium hydrogen carbonate, carmellose sodium, white beeswax, titanium dioxide, ethylcellulose, glyceryl oleate, polysorbate 80, povidone, sucrose, anhydrous colloidal silica, magnesium stearate, talc |                                    |
|                                          | pioglitazone 30 mg                                                                                                                                                                                                          | pioglitazone 45 mg                                                                                                                                                                                                          | pioglitazone placebo |

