**Table (8.4.1) 2 – Description of packaging**

| Placebo packaging from ASSE to W0                                                                             |                                                                                                                                                                                                                                                                                                                                                                                                                |
|----------------------------------------------------------------------------------------------------------------------|----------------------------------------------------------------------------------------------------------------------------------------------------------------------------------------------------------------------------------------------------------------------------------------------------------------------------------------------------------------------------------------------------------------|
| Number of units of the pharmaceutical form per primary packaging                                                     | 1 blister card contains 21 tablets and 7 capsules.                                                                                                                                                                                                                                                                                                                                                             |
| Number of primary packaging per secondary packaging                                                                  | One smaller bag of 5 blister cards with placebo will be packed in one box (4 weeks of treatment + 1 extra-week of treatment).                                                                                                                                                                                                                                                                                  |

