## 10. TREATMENT OF PARTICIPANTS

### 10.1. Treatment administered

Benfluorex, pioglitazone and the placebo will be administered three times per day (from selection to the end of the study): one capsule and one tablet during breakfast, one tablet during lunch and one tablet during dinner.

The usual sulfonylurea treatment will be maintained throughout the study except in case of severe or repeated hypoglycaemia (> 3 episodes in a month). It will not be provided by the Sponsor.

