#### 4.3 Contraindications

- Hypersensitivity to benfluorex hydrochloride or one of its constituents
- Established chronic pancreatitis.

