#### 4.4 Special warnings and special precautions for use

The metabolic disorders in patients treated with Mediator are mainly observed in adults. Prescription of Mediator for children is therefore unjustified.

If, after a treatment period of a few months (3 to 6 months), a satisfactory decrease in serum lipid or glucose concentration is not obtained, complementary or alternative therapeutic strategies are to be envisaged.

The attention of sportsmen and athletes is drawn to the fact that this proprietary medicinal product contains an active substance that may induce a positive reaction in illicit drug screens.

Due to the presence of sucrose, this medicinal product is not to be used in cases of fructose intolerance, glucose and galactose malabsorption syndrome or sucrase-isomaltase deficiency.

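### No eligibility criterion carries the benfluorex label's instruction not to use the sucrose-containing tablet in three sugar-intolerance conditions (minor safety gap)

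*Protocol*

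**What the plan says.** Section 9.2.2 introduces the benfluorex exclusions with "Contraindication to treatment by benfluorex (as referred in the product characteristics, see appendix 6) i.e" and follows with two items: chronic pancreatitis, and known hypersensitivity to the drug or a component. Section 6 gives the same pair, introduced as "the only contraindications to treatment with benfluorex are currently".

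Appendix 6 reproduces the benfluorex label. Its section 4.3 lists "Hypersensitivity to benfluorex hydrochloride or one of its constituents" and established chronic pancreatitis. Its section 4.4, on warnings and precautions, says that because of the sucrose "this medicinal product is not to be used in cases of fructose intolerance, glucose and galactose malabsorption syndrome or sucrase-isomaltase deficiency".

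Table (8.4.1) 1 prints the same excipient list for the active and the placebo benfluorex tablet, ending "polysorbate 80, povidone, sucrose, anhydrous colloidal silica, magnesium stearate, talc". Section 8.3 states that "in the pioglitazone group: 3 tablets of benfluorex placebo and 1 capsule of pioglitazone will be administered per day"; the benfluorex arm takes three benfluorex tablets and a placebo capsule. Section 10.1 says that the study products "will be administered three times per day (from selection to the end of the study".

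**The concern.** The label's instruction is worded as a bar on use, although it stands under warnings rather than contraindications. The list in 9.2.2 is closed by *i.e.* after two items, and no other criterion mentions sugar intolerance. An investigator who works through sections 9.1 to 9.4 is not told to exclude a patient known to have one of the three conditions.

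The double-dummy design extends the question to both arms, because the placebo tablet also contains sucrose. What is at stake is the safety of a small, unquantified group of patients who could be given a tablet that the protocol's own appendix says they should not take.

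**Working it through.** This is a comparison of texts. The plan gives no figure on the point to reproduce.

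**1. Label conditions against the eligibility criteria (sections 9.1 to 9.4, read in full)**

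| Condition | Label section (Appendix 6) | Named in 9.1–9.4? |
|---|---|---|
| Hypersensitivity to drug or constituent | 4.3 | Yes, 9.2.2 |
| Chronic pancreatitis | 4.3 | Yes, 9.2.2 |
| Fructose intolerance | 4.4 | No |
| Glucose-galactose malabsorption | 4.4 | No |
| Sucrase-isomaltase deficiency | 4.4 | No |

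Both section 4.3 items are carried over (2 of 2). None of the three section 4.4 conditions is (0 of 3).

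**2. Who takes the sucrose-containing tablet.** Tablets per day from Table (10.1) 1, with sucrose in both kinds according to Table (8.4.1) 1:

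| Arm and dose level | Active | Placebo | Total |
|---|---|---|---|
| Benfluorex, dose I | 1 | 2 | 3 |
| Benfluorex, dose A | 2 | 1 | 3 |
| Benfluorex, dose B | 3 | 0 | 3 |
| Pioglitazone, any dose | 0 | 3 | 3 |

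Every randomised patient is assigned three such tablets a day, whatever the arm or dose.

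**3. Run-in.** For the run-in pack, Table (8.4.1) 2 states "1 blister card contains 21 tablets and 7 capsules". One card covers a week, so 21 / 7 = 3 tablets a day. The composition of the run-in tablet is not tabulated separately. That it is the same sucrose-containing placebo is a reasonable inference, not a stated fact.

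**4. Does a listed item already cover the three conditions?** The nearest is hypersensitivity to a component. Malabsorption and enzyme deficiency are not hypersensitivity, and the label itself deals with them separately, in 4.4 rather than 4.3. The item in 9.2.2 on uncontrolled, clinically significant disease need not catch an intolerance that is controlled by diet.

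**5. How the protocol treated the comparator's label.** Section 4.3 of the pioglitazone label (Appendix 5) lists hepatic impairment. Section 4.4 of that label adds other evidence of liver disease and an ALT limit of 2.5 times the upper limit of normal. Both additions became criteria, the first in 9.2.2 and the second in 9.4. The protocol therefore did not confine itself to section 4.3 of the labels when it wrote its criteria.

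**6. Statistical effect.** Both arms take the same number of sucrose-containing tablets. Nothing here enters the margin, the standard deviation, the sample size, the type I error or the model for HbA1c.

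**The case against.** The strongest defence is that nothing is misstated. Section 9.2.2 is headed as a list of contraindications, label section 4.3 has exactly two, and both are there. Section 6 agrees. A reader might infer from the closed list that the protocol misquotes the label, but the documents do not support that: the sucrose text lies in 4.4, and the two listed items are right as they stand.

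The instruction is also within the protocol, since Appendix 6 is part of it and the criterion refers to it by number. Several judgement-based criteria could exclude such a patient: the ability to follow study procedures and instructions (9.1.2), likely non-compliance with study medication (9.2.1), and inability to comply with study treatment (9.4), where the 80% to 120% run-in limits are only a particular case. Study instructions include taking sugar for suspected hypoglycaemia (12.2), which may prompt a patient with a known intolerance to speak up.

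All of this stands as mitigation. It would be too strong to say that such a patient positively qualifies; the supportable statement is that the patient is not specifically barred. The compliance criteria depend on the investigator's judgement and do not mention the conditions. The pointer to Appendix 6 concerns contraindications and is then spelled out as two items, so it does not lead the reader to 4.4. The numerical run-in limits, and stopping for an adverse event, act only after tablets have been dispensed.

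**Conclusion.** The gap is real and minor. Sections 9.1 to 9.4 do not carry the label section 4.4 instruction, and a patient with a known diagnosis of one of the three conditions could be entered in either arm without breaching a specific criterion. This rests on the printed criteria, label and tablet composition; only the run-in composition is inferred.

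A reader might want to put numbers on the exposure. The documents do not support them:

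- **A minimum number of tablets taken before inclusion.** At 3 a day, a 28-day run-in gives 3 × 28 = 84 tablets, and 80% of that is 67.2, so 68. But section 8.2.1 allows 4 weeks ± 1 week. The range is 3 × 21 = 63 tablets (80% is 50.4, so 51) to 3 × 35 = 105 tablets (80% is 84). Section 10.4 measures compliance from tablets dispensed and returned, so an unreturned tablet counts as taken.
- **A ceiling on the sucrose dose.** The marketed tablet weighs 700 mg with 150 mg of active drug (Appendix 6, section 2), which leaves 550 mg. That subtraction does not apply to a placebo tablet with 0 mg of active drug, lactose in an unstated amount and no stated weight. The sucrose content appears nowhere.
- **A number of affected patients.** No prevalence is given.

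No such figure is claimed. Nor is there a basis for inferring bias in the HbA1c comparison, since both arms are assigned the same number of tablets.

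**What to change.** Add one non-selection criterion to section 9.2.2: *Known fructose intolerance, glucose-galactose malabsorption or sucrase-isomaltase deficiency (Appendix 6, section 4.4).* Leave the two listed contraindications and the sentence in section 6 as they are. Section 9.4 already reapplies the non-selection criteria at inclusion, so no second change is needed there.

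The criterion can be answered from the medical history taken at the selection visit (Figure (8.2.2) 1 and section 9.5), without a test. The cost is one more history question and some exclusions, assumed to be very few because the protocol gives no prevalence. They would fall before randomisation, so the planned 1000 patients, the 0.4% margin and the analysis are unaffected. Undiagnosed cases would still be missed.

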### 9.3. Inclusion criteria

- Patient still fulfilling all the selection criteria.
- **HbA1c** measured between selection and inclusion (central laboratory, HPLC method) must be  **$> 7\%$  and  $\leq 10\%$** . At least 500 patients will have HbA1c in the range  $[8\% ; 10\%]$ .

### 9.4. Non-inclusion criteria

- Presence of non-selection criteria after the clinical and biological examinations performed since the visit ASSE and particularly if blood pressure is above the upper limit at both the selection and the inclusion visit, the patient must not be included (see section 9.2).
- Patient unable to comply with the study treatment particularly if compliance assessed at the W0 visit of run-in placebo capsules or run-in placebo tablets is  $> 120\%$  or  $< 80\%$ .

- Left Ventricular Ejection Fraction (LVEF) < 40% and any major cardiac pathology discovered at echocardiography according to local assessment (see appendix 16).
- Abnormal biological results:
  - o ALAT > 2.5 times the Upper Limit Normal (ULN) value.
  - o Haemoglobin level < 12 g/dL in men and < 11 g/dL in women.
  - o Creatinine clearance < 30 mL/min according to the Cockcroft and Gault formula (see appendix 15).
  - o Triglycerides > 4 g/L (4,6 mmol/L.)
- Unauthorised concomitant treatments (see appendix 7).

